#### Primary Outcome Measures

To explore users’ acceptance of PRECIOUS system, the following aspects will be assessed:

Usability: 11-item questionnaire (10 items with 5-point Likert scale and 1 item with 10-point Likert scale) to assess users’ interaction with app and system interface.

Satisfaction: 14-item questionnaire (10-point Likert scale) to assess satisfaction with the different modules of the app (physical activity, diet diary), reports, feedback messages, and other interface elements.

Acceptance: 4-item questionnaire (10-point Likert scale) to measure the disposition to use and recommend the system to other patients.

Effectiveness: 15-item questionnaire (10-point Likert scale) to assess engagement, change, and adherence to healthy habits.

In Group 1 (control, treatment as usual), all these aspects will be assessed but with an adaptation of the same questionnaires based on their specific follow-up and the use of the Bodyguard2.

These measures were developed ad hoc for this study, but the usability items are based on the System Usability Scale [16] and acceptance and satisfaction items are based on the Questionnaire for User Interaction Satisfaction 7.0 [17].

#### Secondary Outcome Measures

Additional outcome measures will be included to explore the differences between groups across the sessions. Demographics and clinical data such as date of birth, gender, actual and maximum attained weight, height, number of diets in previous year, and questions related to self-esteem will be registered.

Health-related quality of life will be assessed with the Spanish version of the Short Form (SF)-12v2 Health Survey [18,19], a shorter version of the SF-36v2 Health Survey that consisted of 12 questions (3 and 5-point Likert scale) to measure functional health and well-being from the patient’s point of view. The SF-12v2 covers the same 8 health domains as the SF-36v2: physical functioning, role-physical, bodily pain, general health, vitality, social functioning, role-emotional, and mental health.

Weight management will be assessed with Spanish versions of S-Weight and P-Weight questionnaires [20,21]. P-Weight is a 34-item questionnaire (5-point Likert scale) developed to assess the process of change in weight management. S-Weight consists of 5 mutually exclusive items that allow allocation of participants to one of the five stages of change of the Transtheoretical Model [22] for weight management: precontemplation (not ready), contemplation (getting ready), preparation (ready), action, and maintenance.

The symptoms of depression, anxiety, and stress will be measured with the Spanish version of the Depression, Anxiety, and Stress Scale (DASS) [23]. DASS is a 21-item questionnaire (4-point Likert scale) developed to assess the severity of the core symptoms of depression, anxiety, and stress, and it is not designed as a diagnostic tool. For each scale, it offers a severity rating: normal, mild, moderate, severe, and extremely severe.

Alcohol consumption will be measured with the Spanish version of Alcohol Use Disorders Identification [24,25], a 10-item questionnaire (4-point Likert scale) developed by the World Health Organization as a simple method of screening for excessive drinking and to assist in brief assessment.

Tobacco consumption will be measured with the Spanish version of Fagerstrom Test for Nicotine Dependence [26,27]. It contains 6 items (some with a yes/no response and some with a 4-point Likert scale) that evaluate the quantity of cigarette consumption, the compulsion to use, and dependence.

Sleep quality will be assessed with the Spanish version of the Pittsburgh Sleep Quality Index [28,29], which measures sleep quality and disturbances over a 1-month time interval with 19 items. It assesses the following components: subjective sleep quality, sleep latency, sleep duration, habitual sleep efficiency, sleep disturbances, use of sleeping medication, and daytime dysfunction.

Physical activity will be assessed with the PRECIOUS app in the intervention groups (Groups 2 and 3). Physical activity will be measured with accelerometer data from the patient’s mobile phone. The accelerometer counts the steps walked and provides the patient a graphic result with total accumulated steps and time spent. If the patient cannot wear the mobile phone, the PRECIOUS app allows them to manually introduce the activity performed and it calculates the equivalence in steps.

Nutritional habits will be assessed with the PRECIOUS app in the intervention groups (Groups 2 and 3) with a diary that allows the patient to register the different meals each day.

The PRECIOUS app architecture and the interface of the physical activity and nutritional habits modules includes the four processes of MI (engaging, focusing, evoking, and planning) and MI micro-abilities (open questions, affirmations, reflections, summaries, and offering information to the users with their permission). Figure 1 shows screenshots of the PRECIOUS app. For the control group (Group 1), physical activity and nutritional habits will be assessed with self-reports using a weekly diary on paper. A total of 6 weeks will be registered: 3 weeks at the start of the study and 3 weeks at the end of the study.

To measure cardiovascular activity, the Bodyguard2 (Firstbeat) device will be used. This device works as a Holter measurement and allows recording of 24-hour periods. The Bodyguard2 is a lightweight and unobtrusive device, attached to the chest with two adhesive electrodes, and is reliable for recording heart rate variability (R-R interval) and movement data. A total of 6 days/nights will be registered in the groups: 3 days/nights at the start of the study after the first session (week 1) and 3 days/nights before the last session (week 12). Data collected with Bodyguard2 device will be analyzed with an adaptation of the Lifestyle Assessment Analysis Server Software (Firstbeat) performed by the PRECIOUS consortium partners (Aalto). This software provides a detailed report of the measured period: stress levels, recovery reactions, physical activity, exercise, sleep quality, and expended kilocalories. At the follow-up assessments (Sessions 3 and 5), patients will receive a report accompanied by oral explanations of the results provided by the researcher in charge of the follow-up.

**Figure 1 figure1:**
[figure not shown]
Screenshots of PRECIOUS app: a) home screen, b) physical activity app, c) dietary app.

### Procedure

The study will have a duration of 3 months with the following scheduled follow-up appointments: Session 1 (Week 1) as a baseline, Session 2 (Week 3), Session 3 (Week 5), Session 4 (Week 8), and Session 5 (Week 12). Figure 2 shows a detailed timeline of the procedure and measures assessed in each session. In Session 1, patients will receive a detailed explanation of the study, will be provided with written and oral information, and will give informed consent. They will then answer all of secondary measures in a semistructured interview and then receive the Bodyguard2 device. Patients from the intervention groups (Groups 2 and 3) will be invited to download the PRECIOUS app on their mobile phone and create a user account. Patients from the control group (Group 1) will receive a 3-week paper diary to register physical activity and nutritional habits. They will also follow their treatment as usual for morbid obesity. Specifically, treatment as usual consists of regular follow-ups with the endocrinologist and standard routine tests (blood samples, glucose) and anthropometric measurements carried out by a nurse. Session 1 lasts 1 hour approximately. Sessions 2 and 4 will be telephone follow-ups, lasting a maximum of 10 minutes. Only doubts and questions regarding PRECIOUS will be addressed (specific measures not collected) in telephone follow-ups. In all three groups, the use of the Bodyguard2 device during the 3 days/nights after Session 1 will be verified. In these telephone follow-ups, the researchers and users agree on the day of the next session in the hospital. Session 3 will be focused on discussing the results obtained with Bodyguard2 (only in Groups 2 and 3), to understand users’ preliminary opinions about the PRECIOUS app. In Group 1, the weekly self-reports of physical activity and nutritional habits will be discussed. Session 3 lasts 1 hour approximately. Session 5 will be the last of the study. Primary and secondary measures will be answered, and the results obtained with Bodyguard2 will be discussed. This last session lasts 1 hour and 30 minutes approximately. All the Group 3 follow-ups will be performed following MI principles. In Groups 1 and 2, MI principles will not be applied. MI has the main goal of getting participants to resolve their ambivalence about changing behavior while not evoking resistance. For such purposes, a directive, person-centered counseling style is employed. This approach is intended to elicit behavior change by helping patients explore and resolve ambivalences and understand the discrepancy between participants’ current behaviors in terms of lifestyles and desired goals [13]. The researcher in charge of these groups has specific training to lead MI sessions.

**Figure 2 figure2:**
[figure not shown]
Flowchart of sessions during the pilot test and the measures assessed in each one.

### Statistical Plan

The statistical analysis will consist of intergroup (Groups 2 and 3) descriptive and mean comparison analyses concerning primary outcome measures (usability, user satisfaction, acceptance, and system effectiveness) and overall assessment of the motivational aspects of PRECIOUS. In our pilot test, the method to assess minimal clinically important difference will be employed (distribution-based method, ie, ±1 mean standard deviation) to study differences between groups related to the main primary outcomes [30].

Secondary analyses will describe and explore changes between groups (inter and intra) in the following secondary outcome measures: (1) health-related quality of life using SF12v2), (2) weight management using S-Weight & P-Weight, (3) severity of the core symptoms of depression, anxiety, and stress using DASS, (4) alcohol consumption using Alcohol Use Disorders Identification test, (5) tobacco use with the Fagerstrom Test for Nicotine Dependence, and (6) sleep quality using the Pittsburgh Quality of Sleep Index. For these purposes, correlational, median comparisons, and nonparametric tests (chi-square tests, Mann-Whitney U) will be performed.

Setting the pilot trial sample size in order to minimize overall size has been based on the Kieser and Wassmer approach. They applied the 80% upper control limit approach to sample size calculation and found that a pilot trial sample size between 20 and 40 would minimize the overall sample size for a main study sample size of 80-250, corresponding to standardized effect sizes of 0.4 and 0.7 (for 90% power based on a standard sample size calculation) [31].

All analyses will be carried out using the Statistical Package for Social Sciences, version 19. A 95% confidence interval will be used for all analyses.

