### Hypothesis

Since this is a pilot study aimed at testing the feasibility of using the technology to achieve behavior change, no specific hypotheses have been put forward. Based on previous research on the efficacy of lifestyle apps and MI studies to foster behavior change [9,13-15], it can be expected that intervention groups (Groups 2 & 3) will show a tendency of change towards a healthier lifestyle compared to control group. These changes can be measured with the weight management questionnaires, the substance use/abuse questionnaires, and with several items related to the assessment of one of the main variables of the study (effectiveness).

No preliminary hypotheses have been established about possible differences between intervention Groups 2 and 3. Ideally, both groups will follow PRECIOUS recommendations with no significant differences between them. Thus, the potential benefits of the PRECIOUS app are expected to be achieved without the need for additional support (MI counseling). The PRECIOUS app’s continuous monitoring and feedback, as well as psycho-educational content and messages, are expected to effectively foster healthier lifestyles.

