### Sample, Recruitment, and Study Design

A convenience sample (non-probabilistic) of patients has been recruited from a specialist outpatient consultation (anonymized for peer review). From an initial list of 55 potential participants, 24 (43.6%) were not included in the study because they were not interested or able to follow the full 3-month protocol. A total of 31 patients (71%, 22 women and 29%, 9 men) meeting the following inclusion criteria has been recruited: (1) patients under the care of medical specialists who adhere to national guidelines for morbid obesity and prediabetic condition following the American Diabetes Association criteria of fasting plasma glucose level from 5.6mmol/L (100 mg/dL) to 6.9mmol/L (125 mg/dL), (2) ˃18 years old, (3) body mass index ≥30, (4) understand and complete questionnaires in Spanish language, (5) use multimedia platforms such as personal digital assistants, tablets, laptops, mobile phones, or personal computers on a regular basis, and (6) have Android devices with an Internet connection. The rationale for choosing participants with Android devices is mainly technical because at this stage of the project, only an Android version of the app is available. Patients with the following criteria have been excluded from the study: (1) any mental (eg, cognitive impairment, severe psychopathology not stabilized) or physical condition that could interfere with the successful application of the research protocol, and (2) technological illiteracy or any other condition precluding the use of a mobile phone. Table 1 shows the demographic characteristics of the sample. Potential participants have been invited to take part in the study via telephone contact and have been randomly assigned into three groups:

Group 1: Control group (treatment as usual + Bodyguard2)Group 2: PRECIOUS system (PRECIOUS app + Bodyguard2)Group 3: PRECIOUS system (PRECIOUS app + Bodyguard2 + MI)

**Table 1 table1:** Demographic and health characteristics of the sample.

Characteristic	Group, mean (SD)			
	1 (n=11)	2 (n=10)	3 (n=10)	Total (n=31)
Age, years	37.45 (11.7)	41.9 (6.2)	38.9 (8.2)	39.35 (9)
Weight, kg	129.18 (17.5)	112.5 (11.7)	116.86 (21.3)	119.83 (18.2)
Height, cm	161.45 (9.3)	165.7 (5.5)	166.9 (9)	164.58 (8.3)
Body mass index, kg/m^2^	49.56 (5.6)	40.9 (2.8)	41.68 (4.4)	44.23 (5.9)
Maximum attained weight, kg	131.36 (19)	117.7 (11.5)	125.2 (20)	124.97 (17.7)
Number of diets last year	3.18 (4.2)	2 (3.2)	2.8 (3.1)	2.68 (3.5)

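### Control starts 8.27 kg/m² (1.85 SD) heavier than the app arms, yet the secondary comparisons with control are fixed as unadjusted tests and the imbalance is not acknowledged

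*Protocol article*

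**What the plan says.** Under Sample, Recruitment, and Study Design, patients "have been randomly assigned into three groups". Table 1 in the same section gives mean BMI (SD) of 49.56 (5.6) in Group 1 (control, n=11), 40.9 (2.8) in Group 2 (app, n=10) and 41.68 (4.4) in Group 3 (app plus motivational interviewing, n=10).

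The Hypothesis section puts forward no specific hypotheses but does state a direction: "it can be expected that intervention groups (Groups 2 & 3) will show a tendency of change towards a healthier lifestyle compared to control group".

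The Statistical Plan confines the primary comparison to the two app arms: "The statistical analysis will consist of intergroup (Groups 2 and 3) descriptive and mean comparison analyses concerning primary outcome measures". Control therefore enters only in the secondary part: "Secondary analyses will describe and explore changes between groups (inter and intra) in the following secondary outcome measures". Six questionnaire domains follow: quality of life, weight management, depression/anxiety/stress, alcohol, tobacco and sleep. The methods for them are then named: "For these purposes, correlational, median comparisons, and nonparametric tests (chi-square tests, Mann-Whitney U) will be performed". The section ends with "A 95% confidence interval will be used for all analyses". The Procedure section has the secondary measures taken at Session 1 and again at Session 5 (week 12).

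**The concern.** The imbalance was already tabulated when the article fixed its methods. The tests it names for comparing groups have no place for a covariate. If BMI is related to an outcome such as physical quality of life, sleep or weight-management behaviour, a raw difference between control and the app arms mixes the starting difference with any effect of the app. Control has no role in the primary comparison, so the secondary analyses are where evidence on app versus usual care would come from. The Limitations section covers representativeness, app updates, questionnaire burden and technological literacy, but not this gap.

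**Working it through.** **Inputs.** BMI means, SDs and group sizes from Table 1. The documents give no correlation between BMI and any outcome, so it is an assumption, shown over a range.

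**Reproducing Table 1's total.**
- Mean: (11×49.56 + 10×40.9 + 10×41.68)/31 = 44.22.
- Within-group sum of squares: 10×5.6² + 9×2.8² + 9×4.4² = 558.4. Between-group: 488.4.
- Total SD: √((558.4 + 488.4)/30) = 5.91.
- Table 1 states 44.23 (5.9), so the rows are consistent. Mean weight over mean height squared gives 49.56, 40.97 and 41.95, so a misprinted BMI row is unlikely.

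**Size of the imbalance.**
- Pooled app mean: (40.9 + 41.68)/2 = 41.29. Gap: 49.56 − 41.29 = 8.27 kg/m².
- Pooled within-group SD: √(558.4/28) = 4.47. Standardised gap: 8.27/4.47 = 1.85. On the total-sample SD of 5.9, which the gap itself inflates, it is 1.40.
- Three-group F: (488.4/2)/(558.4/28) = 12.25, p = 0.00015.
- Groups 2 and 3 differ by only 41.68 − 40.9 = 0.78 kg/m².

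**Reading A: raw week-12 scores compared.** With no app effect and within-group correlation r, the spurious difference is r × 1.85 SD. Simulated Mann-Whitney false-positive rates (4,000 runs per setting, control 11 v both app arms 20, nominal 5%):

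| r | Spurious difference (SD) | Mann-Whitney | Linear model with BMI |
|---|---|---|---|
| 0 | 0 | 4.6% | 4.8% |
| 0.1 | 0.19 | 7.4% | 5.8% |
| 0.2 | 0.37 | 15% | 5.7% |
| 0.3 | 0.56 | 28% | 4.9% |
| 0.4 | 0.74 | 45% | 5.7% |

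The plan does not say that the app arms are pooled. Tested separately, Group 1 v 2 and Group 1 v 3 give about 12% and 9% at r = 0.2, 21% and 15% at 0.3, and 34% and 24% at 0.4.

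**Reading B: change scores compared.** Assume that BMI relates equally to the Session 1 and week-12 scores and that these correlate 0.6 within groups. The r × 1.85 SD term is then in both scores and subtracts out. Simulated Mann-Whitney rates stay at 4.3–5.3% for r from 0 to 0.4. Bias remains only through regression to the mean or if BMI predicts 12-week change.

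**What adjustment does.** Under the Reading B assumptions, adjusting the week-12 score for the Session 1 score alone leaves a difference of r × 1.85 × (1 − 0.6). At r = 0.3 this is 0.22 SD, against 0.56 SD for the raw comparison. Most of the bias goes, but not all, which is why a BMI-adjusted analysis should stand beside it.

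**Price of adding BMI.** Contrast sum of squares: 8.27²/(1/11 + 1/20) = 485.4. Share of BMI variance explained by control v app: 485.4/(558.4 + 488.4) = 0.464. Variance inflation: 1/(1 − 0.464) = 1.87. Standard error factor: √1.87 = 1.37, so about 37% wider.

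**The case against.** The strongest reply is that the plan speaks of changes between groups, within and between. A Mann-Whitney test on change scores does use the Session 1 score, and Reading B shows that a stable BMI link then largely cancels. This stands. A reader might infer that the named tests cannot use the baseline score, or that false-positive rates of 15–45% apply to the plan as written. The text supports neither: those rates need raw week-12 scores, a correlation of 0.2 or more, and pooled app arms. The range also cannot be carried to all six domains; nothing in the article links BMI to alcohol or tobacco use.

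Second, the pilot's main aim is satisfaction, usability and acceptability, and its primary comparison excludes control. BMI and weight are not among the six listed secondary outcomes. This stands too, and it lowers the severity.

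Third, an article condenses its analysis plan, and covariate models are often left to the fuller document. That would answer mere silence. Here the article names the tests, prints the imbalance and omits it from its limitations.

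Fourth, BMI adjustment is costly. The standard error is wider, BMI overlap between 49.56 (5.6) and 40.9 (2.8) is thin, and the slope must be estimated from 31 patients. This stands as a reason to make it a sensitivity analysis and not the sole replacement.

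Finally, p = 0.00015 might tempt a reader to infer that allocation went wrong. The documents do not show that; a gap this large is improbable under random assignment but can occur.

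**Conclusion.** The point holds in moderate form. The gap of 8.27 kg/m² (1.85 pooled within-group SD) follows from Table 1 without assumption. The tests named for the secondary outcomes do not adjust for it, and the article does not acknowledge it. How far a control comparison is distorted rests on two things the documents leave open: whether raw or change scores are compared, and how strongly BMI relates to each outcome. For raw scores the false-positive rate runs from about 5% (r = 0) to 45% (r = 0.4) under 11 v 20; for change scores with a stable BMI link it stays near 5%. The direction is not fixed, so an app effect could be imitated or masked.

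A reader might extend this to the whole trial. The documents do not support that: the primary comparison of Groups 2 and 3 is not affected, and the control comparisons are exploratory.

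**What to change.** 1. For each secondary measure, analyse the week-12 score by arm, adjusted for the Session 1 score of the same measure (ANCOVA, rank-based or ordinal where feasible). Report estimates with 95% confidence intervals for Group 2 v 1 and Group 3 v 1.
2. Add a sensitivity analysis that also adjusts for baseline BMI. Report with it the wider standard error (about 37%) and the limited BMI overlap, so that a shift in the estimate is not over-read.
3. State the imbalance in the Limitations section as a restriction on any comparison with control.

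The cost is wording and analysis time. Session 1 scores and BMI are already in hand, so no new data are needed. Adjusting for the Session 1 score normally gains precision; the BMI adjustment loses some on the control contrast. With 31 patients an ordinal model for the five weight-management stages may not be stable, in which case a descriptive report of that measure is enough.

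### The secondary analysis plans within-group change but names only independent-sample tests (chi-square, Mann-Whitney U), although Session 1 and Session 5 values are paired

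*Protocol article*

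**What the plan says.** The Statistical Plan of the protocol article sets the target: "Secondary analyses will describe and explore changes between groups (inter and intra) in the following secondary outcome measures". Six groups of instruments follow, among them S-Weight and P-Weight. The next sentence names the methods: "For these purposes, correlational, median comparisons, and nonparametric tests (chi-square tests, Mann-Whitney U) will be performed". The section ends: "A 95% confidence interval will be used for all analyses".

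The Procedure section fixes when these outcomes are measured. At Session 1 (Week 1): "They will then answer all of secondary measures in a semistructured interview". At Session 5 (Week 12): "Primary and secondary measures will be answered". Patients "have been randomly assigned into three groups", and Table 1 gives 11, 10 and 10 per group, 31 in all.

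On the stage-of-change outcome, the Secondary Outcome Measures section says: "S-Weight consists of 5 mutually exclusive items that allow allocation of participants to one of the five stages of change". The stages run in order from precontemplation to maintenance.

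**The concern.** The intra-group half of the aim compares each patient with himself or herself 11 weeks later. Mann-Whitney U and Pearson chi-square treat the two sets of values as if they came from different people. They therefore keep the between-patient variation that pairing removes. The opening words of the methods sentence tie the list to both kinds of comparison, and no paired test appears in it.

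The stake is a missed change. Whether the system triggers behaviour change is one of the stated objectives, and the Hypothesis section names the weight-management questionnaires as one way to measure it. With 10 or 11 patients per arm, a test that discards the pairing can make a real within-arm change look absent. That could mislead the design of a main trial. For S-Weight there is a second loss: chi-square also ignores the order of the stages.

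**Working it through.** The article states no power or size for the secondary tests, so there is no figure of its own to reproduce on this point. Its sample-size paragraph concerns a future main trial and is not used here.

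**Inputs from the article.** Two measurements per patient (Sessions 1 and 5); arms of 11, 10 and 10; five S-Weight stages; two-sided 0.05, read from the 95% interval statement.

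**Assumptions, because the article gives none.** Normal scores with equal SD at both sessions; pre-post correlation ρ from 0 to 0.8; shifts of 0, 0.5 and 0.8 SD; stage distributions as given below.

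**1. Why pairing matters.** The difference between sessions has SD √(2(1−ρ)) in units of the score SD. A 0.8 SD shift is therefore a standardised paired effect of 0.8/√(2(1−ρ)):
- ρ = 0: 0.8/1.414 = 0.57
- ρ = 0.3: 0.8/1.183 = 0.68
- ρ = 0.5: 0.8/1.000 = 0.80
- ρ = 0.7: 0.8/0.775 = 1.03

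A paired test gains from this. An independent-sample test works as if ρ were 0.

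**2. Within-arm simulation.** n = 10, 6,000 runs per setting, exact p-values. Each cell gives Mann-Whitney U against Wilcoxon signed-rank.

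| ρ | False-positive rate | Power, 0.5 SD | Power, 0.8 SD |
|---|---|---|---|
| 0 | 3.6% vs 4.5% | 16% vs 16% | 36% vs 36% |
| 0.3 | 2.0% vs 4.9% | 13% vs 22% | 34% vs 46% |
| 0.5 | 0.7% vs 4.6% | 10% vs 28% | 33% vs 60% |
| 0.7 | 0.2% vs 4.9% | 8% vs 44% | 31% vs 82% |
| 0.8 | 0.1% vs 5.2% | 6% vs 59% | 30% vs 93% |

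The share of signed-rank power lost is 1 − (Mann-Whitney power / signed-rank power), from unrounded values. At 0.8 SD:
- ρ = 0.3: 1 − 0.337/0.463 = 27%
- ρ = 0.5: 1 − 0.325/0.600 = 46%
- ρ = 0.7: 1 − 0.312/0.816 = 62%

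At 0.5 SD the losses for the same correlations are 40%, 66% and 82%. At ρ = 0 there is practically no loss.

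**3. S-Weight between arms.** Three arms by five stages is 15 cells: 31/15 = 2.07 expected per cell on average. With equally common stages it is 11/5 = 2.2 or 10/5 = 2.0. In 4,000 simulated tables per setting, 97–100% of cells had an expected count below 5. The chi-square false-positive rate was 3.0–4.6%, so it was not inflated. For power, the assumed stage distributions were 5/30/40/20/5% in the control arm and 2/10/28/40/20% in the intervention arms:
- three arms: chi-square 20%, Kruskal-Wallis (which uses the order) 42%
- two arms of 10: chi-square 18%, rank test 38%

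**4. S-Weight within an arm.** n = 10, 2,000 runs, latent shift 0.8 SD, first-session stages distributed as in the control arm above. Chi-square against exact signed-rank:
- ρ = 0.3: 12.5% vs 29%
- ρ = 0.5: 11.6% vs 36%
- ρ = 0.7: 9.8% vs 48%

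With no shift both tests rejected in under 2% of runs, so neither overstates change.

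**The case against.** The sentence is one collective list for six kinds of outcome and two kinds of comparison, and it assigns no test to either. The list also contains median comparisons, which could include a paired procedure in a full plan that is not shown. The analyses are exploratory, and the article says that "no specific hypotheses have been put forward". The expectation it does voice is of change relative to control, a between-arm question that Mann-Whitney can serve.

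Much of this stands. It limits the point to the intra-group comparisons and to S-Weight, and it lowers the weight. It does not remove the mismatch: the article itself sets within-group change as a target, says which tests serve it, and names none that fits paired data. A generic reference to comparing medians does not supply one.

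A reader might infer four stronger points, and none is supported:
- **Mann-Whitney is wrong with three arms.** It is valid for any two arms, including on change scores. Each pairwise test kept its size (4.0–4.2%). Group 1 against Group 2 had 37% power, the same as Kruskal-Wallis, when both intervention groups were shifted by 0.8 SD. Testing all three pairs unadjusted gives about 10% familywise error, which is minor in an exploratory pilot, and the article does not say that all three will be tested.
- **The sparse chi-square table gives too many false positives.** The simulation shows otherwise.
- **Most of the power is always lost.** That depends on the correlation; at 0 nothing is lost.
- **Mann-Whitney cannot meet the 95% interval statement.** A Hodges-Lehmann interval can accompany it.

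**Conclusion.** Wrong as written, for secondary outcomes only. Applied to within-arm change at about 10 per arm, the named tests are conservative. For Mann-Whitney the loss against signed-rank is none at correlation 0. At a 0.8 SD shift it is about a quarter at 0.3, nearly half at 0.5 and over 60% at 0.7, and the proportional loss is larger for a smaller shift. For S-Weight, ignoring stage order about halves power between arms in the assumed examples.

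The direction is firm, because positive correlation between repeat questionnaires in the same people is plausible and any positive correlation costs power. The size rests on the assumed correlation, normal scores, chosen shifts and stage distributions. The error risks missed change, not false claims of benefit. It does not touch the primary outcomes or the between-arm use of Mann-Whitney, so it ranks below a must-fix.

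**What to change.** Replace the single list of tests with one that assigns a method to each comparison:
- **Within group, scores:** Wilcoxon signed-rank on Session 5 minus Session 1, with a Hodges-Lehmann estimate and 95% interval.
- **Within group, S-Weight stage:** a marginal homogeneity test or exact signed-rank.
- **Between arms, scores:** keep Mann-Whitney U, stated to be on change scores, with a Hodges-Lehmann interval.
- **Between arms, S-Weight stage:** an ordinal or exact test in place of the asymptotic Pearson chi-square.

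The cost is a few sentences in the Statistical Plan. The procedures are standard and need no new data or visits. The change should be recorded before the Session 5 results are analysed, after confirming that the stated software version provides the exact tests and intervals.
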